### Sample size calculation and power

We consider the development of ROP a competitive outcome with mortality due to its late onset during postnatal development. The combined variable death or ROP was considered the primary study variable. The incidence of death or ROP in our center in ≤28 weeks is 41%. A 50% reduction in the incidence will be considered clinically significant, so considering a significance level of 0.05 and a power of 0.8, the calculated sample size is 122 patients. Assuming a drop ratio of 10%, 134 patients will be recruited for the study (67 in each group).

University and Polytechnic Hospital La Fe is a tertiary center with 6,000–6,500 births annually. In addition, two other recruiting centers, University Clinical Hospital of Santiago (2,000–2,200 births annually) and Maternal and Child University Hospital Complex of Las Palmas (4,500–4,800 births annually), are included in the study, so we estimate that the sample size could be accomplished in the three years of the study duration.

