### Statistical analysis

The following sets of analyses are planned: (1) All included patients, regardless of whether they were transfused or not; (2) All included patients who received transfusions, as per intention-to-treat (including intervention group patients who received adult donor blood transfusions due to unavailability of umbilical cord blood); (3) All included patients who received transfusions as per protocol (excluding intervention group patients who received adult donor blood transfusions). Secondary analyses will also examine the effect of the two treatment strategies on the described secondary variables. An interim analysis of the results will be conducted once half of the sample has been collected to assess the presence of any relevant safety or mortality outcomes. An external committee will be proposed to perform the calculations while maintaining blinding until evaluation.

Categorical variables are described with each category's numerical count (percentage). If the application assumptions are met, they are compared with Pearson's chi-square test, and if not, Fisher's exact test. Continuous variables are represented with Tuckey box plots. If the constant variables are standard (*p* > 0.05 in the Shapiro–Wilk test), they are described with the mean ± standard deviation. They are compared using Student's *t*-test, first testing the hypothesis of equality of variances using Levene's test. If abnormal, they are described with a median (p25, p75) and compared with the nonparametric Mann–Whitney *U*-test. Comparison between both groups of repeated measures over time is performed by a two-way analysis of variance (ANOVA) test, first testing Mauchly's sphericity hypothesis and rejecting it with *p* < 0.05. Survival times are expressed with their median [95% confidence interval (95% CI)], and between-group comparison is performed with the log-rank test. Throughout the study, a *p* < 0.05 is accepted as the limit of statistical significance. The magnitude of the effect is quantified with the risk difference (expressed as a percentage), and its precision is indicated with the 95% CI.

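### 122 patients give about 70% power, not 80%, under the two-sided test planned; with the stated inputs the figure is reached only by a one-sided 5% calculation

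*Protocol article*

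**What the plan says.** In the protocol article, the section on sample size calculation and power takes the combined variable death or ROP, with an incidence of 41% at the sponsor's centre. On the effect it says: "A 50% reduction in the incidence will be considered clinically significant". The result follows: "considering a significance level of 0.05 and a power of 0.8, the calculated sample size is 122 patients". A 10% loss then brings the total to 134, or 67 per group. The section does not state the sidedness of the test or the formula used.

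The statistical analysis section says that categorical variables, where the assumptions are met, are "compared with Pearson's chi-square test, and if not, Fisher's exact test". It sets p < 0.05 as the limit of significance throughout the study. The effect is to be given as a risk difference, and "its precision is indicated with the 95% CI". No one-sided test is mentioned anywhere.

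**The concern.** The section gives every input needed to recompute the sample size, and a conventional two-sided calculation does not return 122. It returns at least 30 more patients. A one-sided 5% calculation lands on or next to 122, which suggests that the trial was sized for one test and will be analysed with another.

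What is at stake is the stated power, which is the justification for the trial's size. If the true power is about 0.70, the risk of missing a halving of death or ROP is half as large again as the protocol says (30% against 20%). A non-significant result could then be read as stronger evidence against the treatment than the design can supply.

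**Working it through.** **Inputs (protocol article).** p1 = 0.41 and p2 = 0.41 × 0.5 = 0.205, so the difference is 0.205; α = 0.05; power 0.80 (all from the sample size section). Allocation is 1:1 (study design section).

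Normal quantiles: 1.645 for one-sided 0.05, 1.960 for two-sided 0.05, and 0.842 for 80% power.

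**Formulas for n per group.**
- Unpooled: (zα + zβ)² × [p1(1−p1) + p2(1−p2)] / (p1−p2)²
- Pooled: [zα√(2p̄(1−p̄)) + zβ√(p1(1−p1) + p2(1−p2))]² / (p1−p2)², with p̄ = 0.3075
- Arcsine: 2[(zα + zβ)/h]², with h = 2·arcsin√p1 − 2·arcsin√p2 = 1.3898 − 0.9397 = 0.4501

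Components: p1(1−p1) = 0.2419; p2(1−p2) = 0.1630; (p1−p2)² = 0.0420; 2p̄(1−p̄) = 0.4259.

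**Reproducing the plan's figure (one-sided 0.05, (zα + zβ)² = 6.183).**
- Unpooled: 6.183 × 0.4049 / 0.0420 = 59.6 per group
- Pooled: 61.6 per group
- Arcsine: 2 × 6.183 / 0.4501² = 61.04 per group; 61 × 2 = 122

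**The same inputs with a two-sided 0.05 ((zα + zβ)² = 7.849).**
- Unpooled: 7.849 × 0.4049 / 0.0420 = 75.6, so 76 per group and 152 in total
- Arcsine: 2 × 7.849 / 0.4501² = 77.5, so 78 per group and 156 in total
- Pooled: 78.4, so 79 per group and 158 in total
- Pooled with continuity correction: 88 per group and 176 in total

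Rounding the intervention rate does not close the gap. The pooled two-sided total is 150 at 20% and 166 at 21%.

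**Power at the planned sizes.** These are sums over all pairs of binomial outcomes at 0.41 and 0.205.

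| n per group | Chi-square, two-sided 0.05 | Same statistic, one-sided 0.05 | Fisher, two-sided |
|---|---|---|---|
| 61 (122 in total) | 0.697 | 0.803 | 0.628 |
| 67 (134, no loss) | 0.740 | 0.838 | 0.678 |
| 78 (156 in total) | 0.803 | – | – |

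The normal approximation agrees at 61 per group: 0.694 two-sided and 0.797 one-sided.

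**Effect detectable with 80% power.** At 61 per group, the two-sided chi-square test reaches 0.80 when p2 = 0.182. The relative reduction is (0.41 − 0.182)/0.41 = 56%, against the 50% stated.

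**Loss allowance.** 122 × 1.1 = 134.2, which is how 134 arises. To keep 122 after a 10% loss takes 122/0.9 = 135.6, that is 136. Recruiting 134 leaves 134 × 0.9 = 120.6.

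**The case against.** The protocol never uses the term two-sided, so that reading is an inference. It is a strong one: the Pearson chi-square statistic does not distinguish direction, and a 95% interval pairs with a two-sided 5% test. If a one-sided test was intended, the sample size section would have to say so and the analysis section would have to change. The text needs correcting either way.

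The one-sided origin of 122 is not proven. Rounded up per group, the one-sided formulas give 120, 124 and 124, and 122 needs 61.04 to be rounded down to 61. A different control rate could also produce a total of this size with a two-sided test; a halving from 48%, for instance, gives 124 by the pooled formula. This stands as a caution about the cause. It does not help the stated figure, because no two-sided formula returns 122 from 41% and a 50% reduction.

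The Fisher figures carry little weight. Fisher's test is only the fallback, and expected counts at these rates are well above 5 (61 × 0.3075 = 18.8 events per group under a common rate). The chi-square figures are the relevant ones.

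The loss step is minor. Adding 10% is a common shortcut, it costs two patients, and exact power at 60 per group is 0.698, practically the same as at 61.

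Finally, the planned confidence interval will show readers how imprecise the result is, which limits over-reading of a null result. It does not make the stated power correct.

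**Conclusion.** The point holds, and the statement is wrong as written. Under the two-sided 5% chi-square test that the analysis section describes, 122 patients give a power of about 0.70 for 41% against 20.5%, some ten percentage points below the stated 0.8. The trial would need 152 to 158 evaluable patients for 80%, so 122 is 30 to 36 short. Recruiting 134 with no loss at all still gives only 0.74.

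This rests on the protocol's own rates, on 1:1 allocation, and on reading the planned test as two-sided. It does not depend on which standard formula was used or on why 122 was obtained. It applies to death or ROP, the variable used for sizing.

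**What to change.** Keep 134 and correct the statement. Suggested wording for the sample size section: *With 134 infants recruited and 10% loss, about 120 are evaluable. For death or ROP, a two-sided chi-square test at the 0.05 level then has about 70% power to detect 41% against 20.5%, and about 80% power to detect 41% against 18%.*

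Write two-sided beside the 0.05 in both the sample size and the analysis sections, and name the formula or software used. If 122 came from a different control rate or from a one-sided test, say so. A one-sided choice would also have to be carried into the analysis section.

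The cost is wording only. No extra infants are needed and conduct does not change, but the stated power becomes less favourable. If the sponsor prefers to keep 80% power for a 50% reduction, the price is recruitment: 158/0.9 = 175.6, so 176 infants in place of 134.

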### Recruitment and consent

Once a potential study participant has been identified, investigators will ask for informed consent from the infant's parents or legal guardians. Written informed consent will be obtained prenatally before delivery, reviewed, signed, and dated by the investigator and parents/legal guardians. The patient information sheet will include all the complementary tests carried out during the study.

### Randomization and blinding

Randomization will be done just before birth and generated by random numbers using the R® 3.5.1 software (R Development Core Team, Auckland, New Zealand). Patient numbers will be assigned sequentially by order of entry into the study. Randomization will be stratified into two groups by gestational age (GA) (23–25 and 26–28), using block randomization. The Biostatistics Unit will provide a randomization list for the corresponding Neonatology Service containing the patient number and another for the Blood Bank Service holding the related treatment branch and the patient number. The neonatologist in charge of the patient will assign the patient a number for the study, ensuring that it has not been given to any other patient. Once the number has been provided, it will be sent to the Blood Bank, responsible for keeping the randomization list containing all the information about it.

The Blood Bank will receive the UCB from the delivery room. It will verify that it meets the quality criteria established by the Blood Bank and aliquot it into one or several units of blood, depending on the volume available. Once a transfusion is prescribed for a participating patient, the Blood Bank will dispense either UCB or RBC according to the assigned group in the same container bag typically used in the Neonatology Unit to be indistinguishable from guaranteeing the blinding. The neonatologist will remain blind to the randomization group, as will the nursing staff and specialists in charge of patient care.

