## Abstract

**Background:**

Currently, the treatment of anemia in preterm infants is based on packed red blood cell (RBC) transfusions from adult donors. Oxygen (O2) is mainly transported to the tissues bound to hemoglobin (Hb). In extremely low gestational age neonates (ELGANs), fetal hemoglobin (HbF), which has a higher affinity for O2, represents up to 95% of circulating hemoglobin. During the first month of life, the majority of ELGANs will require an adult-donor RBC transfusion causing HbF levels to rapidly drop. HbA releases 50% more oxygen in peripheral tissues than HbF. Increased release of O2 in the retina is one of the main factors related to the development of retinopathy of prematurity (ROP). Collecting umbilical cord blood and using autologous umbilical cord whole blood (UCB) transfusions would contribute to maintaining physiological HbF concentrations in newborns and avoid oxygen-in-excess derived damage.

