### Study population

Inclusion criteria: Preterm infants with GA ≤28 + 6 weeks of GA.

Exclusion criteria are one or more of the following: major congenital malformations, monochorionic twin pregnancy, chromosomal abnormalities, hemoglobinopathies, isoimmunization, critical condition at birth with a predicted fatal outcome, and refusal to participate and sign the informed consent.

Patients will be managed according to the usual protocols regarding oxygenation limits. The enrolled patients’ targeted oxygen saturation range will be 91%–95%. Transfusion thresholds will be carried out according to local guidelines.

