### Intervention

Patients will be randomized to receive either whole UCBa, intervention group, or standard adult-donor packed RBC, control group. For patients with anemia requiring blood transfusion according to the Spanish Society of Neonatology's standards Committee threshold's recommendations (30), the responsible physician will make the corresponding request for transfusion indicating the volume needed. The Blook Bank will supply UCBa or RBC according to the patient's group, but bag labeling will be indistinguishable. In case there is not enough UCBa, RBC will be administered. As the maximum storage of UCB is 35 days, both groups will receive adult-donor RBC concentrates after this age. Transfusion's traceability will always be maintained through the e-Delphyn Transfusion Service software. UCB extraction and storage protocols are detailed in Appendix I.

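### Randomising before birth brings in infants whose treatment cannot differ by arm; this dilutes the all-randomised comparison, and neither the sample size nor any listed analysis set deals with it

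*Protocol article*

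**What the plan says.** Timing (Randomization and blinding): "Randomization will be done just before birth".

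When the arms part (same section): "Once a transfusion is prescribed for a participating patient, the Blood Bank will dispense either UCB or RBC according to the assigned group". Before that the Blood Bank receives the cord blood, and "It will verify that it meets the quality criteria established by the Blood Bank". Appendix I lists the tests: blood group, antibody screen, infection tests and blood culture.

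When they do not part (Intervention): "In case there is not enough UCBa, RBC will be administered". Cord blood keeps for at most 35 days, and "both groups will receive adult-donor RBC concentrates after this age".

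How many infants are transfused (Abstract, Background): "During the first month of life, the majority of ELGANs will require an adult-donor RBC transfusion". No percentage is given, nor the share of infants with a usable cord unit.

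One exclusion criterion (Study population) can be judged only once the infant is born: "critical condition at birth with a predicted fatal outcome".

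The Sample size section applies a 50% reduction to a 41% rate of death or ROP among all infants of 28 weeks or less at the centre. It allows 10% for dropout and nothing for infants who cannot receive the intervention.

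The Statistical analysis section lists three sets and names none as primary. The first is "All included patients, regardless of whether they were transfused or not". The second is transfused infants as randomised, including intervention infants who got adult blood because no cord blood was available. The third removes intervention infants who received adult blood, with no matching exclusion among controls.

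**The concern.** The Introduction gives the aim as the effect of autologous cord blood transfusion against adult-donor red cells on ROP. Allocation is fixed before anyone knows whether the infant will be transfused or will have a usable unit. An infant who is never transfused, dies before a first transfusion, or has no released unit gets the same treatment in either arm. Such infants add noise and no contrast.

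At stake is power for the trial's own question. The all-randomised comparison carries the full dilution, the second set carries part of it, and the third loses comparability between arms. The Discussion points to the analysis sets as the answer to short cord volumes, but none of the three is the comparison in which the two products can actually differ.

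A smaller consequence is that infants excluded as critical at birth leave after a number has been used, which disturbs the blocks within the gestational-age strata.

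**Working it through.** **Inputs from the protocol article.** Control risk 0.41; 50% relative reduction, so 0.205; significance level 0.05; power 0.8; 122 evaluable infants (61 per arm), 134 with dropout; 1:1 allocation.

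**Assumption, not in the document.** q is the share of randomised infants who are transfused by day 35 and have a released unit of sufficient volume. Range shown: 0.9 to 0.5.

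**Formula.** Two proportions, normal approximation, pooled variance under the null, no continuity correction:

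n per arm = {[z_a √(2p̄(1−p̄)) + 0.8416 √(p1(1−p1)+p2(1−p2))] / (p1−p2)}², with p̄ the mean of p1 and p2. Power is the same expression solved for the second normal deviate.

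**1. The plan's own figure.** With p1 = 0.41 and p2 = 0.205, √(2p̄(1−p̄)) = 0.6526 and √(p1(1−p1)+p2(1−p2)) = 0.6363.
- One-sided (z_a = 1.645): (1.0735 + 0.5355)/0.205 = 7.85, squared 61.6, so 62 per arm, 124 in total. This is within 2 of the stated 122.
- Two-sided (z_a = 1.96): (1.2791 + 0.5355)/0.205 = 8.85, squared 78.4, so 79 per arm, 158 in total.

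The starting point with 61 per arm is therefore 0.80 one-sided and 0.69 two-sided before any dilution. The analysis section reads as two-sided, so two-sided power is used below.

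**2. Dilution when randomising before birth.** If exposable infants have their risk halved and all infants share the 41% risk, the intervention-arm risk is 0.41 × (1 − 0.5q). Example, q = 0.8: 0.41 × 0.6 = 0.246, a 40% reduction overall.

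**3. Same cohort, exposable infants only.** 0.41 against 0.205 with 61q per arm. Example, q = 0.8: 48.8 per arm.

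| q | Reduction over all randomised | Power, all randomised (61 per arm) | Power, exposable only (61q per arm) | Evaluable N for 80% power, all randomised | Infants needed to yield 158 exposable (158/q) |
|---|---|---|---|---|---|
| 1.0 | 50% | 0.69 | 0.69 | 158 | 158 |
| 0.9 | 45% | 0.59 | 0.65 | 198 | 176 |
| 0.8 | 40% | 0.49 | 0.60 | 256 | 198 |
| 0.7 | 35% | 0.39 | 0.54 | 340 | 226 |
| 0.6 | 30% | 0.30 | 0.48 | 470 | 264 |
| 0.5 | 25% | 0.22 | 0.41 | 686 | 316 |

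The exposable comparison has more power at every q below 1, although it uses fewer infants. Neither column restores 0.80.

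**4. Unequal baseline risk.** Hold the overall risk at 41% and give unexposable infants an assumed risk of 10% to 20%. At q = 0.8 the overall reduction is then 48% to 45% instead of 40%. If exposable infants have an assumed risk of 50%, power is 0.67 (all randomised) against 0.73 (exposable) at q = 0.8, and 0.42 against 0.60 at q = 0.6. The loss is smaller; the direction is unchanged.

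**5. What each listed set contains.**
- First: all randomised, so the full dilution.
- Second: transfused infants. The arms are identical and orders are blinded up to the first transfusion, so dropping the never-transfused does not depend on arm. Infants without a unit stay in.
- Third: exclusion from one arm only, so the arms are no longer comparable.

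**The case against.** Randomising at birth is a legitimate choice. The analysis section speaks of comparing treatment strategies, and the 41% comes from all infants of 28 weeks or less, which suits an all-randomised population. That stands as a defence of the first set. It does not reach the sample size, which assumes the full 50% reduction in a population where some infants cannot benefit.

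q may also be high. The Introduction cites collections sufficient for one to two transfusions, and the Discussion expects early needs to be met. At q = 0.95 the powers are 0.64 and 0.67, so the gap would be small. This stands, and it is why the size of the loss is conditional.

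A third objection is that the gain in the table comes from restricting the comparison to exposable infants in both arms, not from the timing itself. Largely true: a symmetric subset under the present timing gives the same power, provided units are checked in both arms. But no listed set is that subset.

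Finally, moving allocation to the Blood Bank would let the holder of the arm list judge eligibility, which threatens concealment. This stands and shapes the fix.

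Four stronger readings are tempting but unsupported:
- That randomising before birth biases the result. It dilutes the difference; the all-randomised comparison stays valid for the strategy. Exclusions at birth by blinded staff unsettle the blocks but do not bias.
- That the second set is as unsafe as the third. Its selection precedes any difference between arms.
- That a null result could not be told apart from non-delivery. Number and volume of transfusions and HbF levels are recorded outcomes.
- That the whole shortfall from 0.80 is dilution. The step from 0.80 to 0.69 is the one-sided against two-sided matter, which is separate.

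**Conclusion.** The point holds as a weakness of design and analysis-set definition that should be corrected. Any share of infants who cannot receive cord blood dilutes the all-randomised difference; the sample size makes no allowance for it, and none of the three sets isolates the comparison that the stated aim needs.

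Its size cannot be fixed from the document because q is not given. The power range of 0.59 to 0.22, against 0.65 to 0.41 for exposable infants, rests on q between 0.9 and 0.5, a 41% risk shared by all infants, a halving of risk in exposable infants, and a two-sided test. Lower risk in unexposable infants reduces the loss. Adult-donor top-ups, which the Discussion expects, are a further dilution not counted here.

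**What to change.** **Preferred change (Randomization and blinding).** Keep prenatal consent and cord collection for all infants. The Blood Bank records release of each unit, against volume and quality criteria set in advance, without reference to the allocation list and before any number is assigned. The blinded neonatology team, not the Blood Bank, then confirms the exclusion criteria and assigns the next number in the gestational-age stratum at the first transfusion order by day 35 for which a released unit is on record. The number goes to the Blood Bank as now. Consented infants who are not randomised appear in the flow chart.

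**If randomisation stays before birth.** Define the main efficacy comparison identically in both arms as infants with a released unit who are transfused by day 35, and report it alongside the all-randomised analysis. State that units are collected and checked in both arms. Restate the power of the all-randomised analysis for the diluted effect, with a justified q.

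**Cost.** One amendment; the lists, the cord units and the staff are already in place. Fewer infants are randomised per consent, or recruitment takes longer: the last column of the table shows the evaluable infants needed, before dropout, to yield 158 exposable ones. The 41% control rate must be re-estimated for exposable infants. With later randomisation the result no longer describes a strategy for all births. Dilution by adult-donor top-ups remains under either option.

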## Methods and analysis

### Study design

To test the hypothesis, we have designed a randomized, multicenter, double-blinded trial to evaluate the effect of UCBa transfusion on the development of ROP compared to transfusion of adult-donor RBC in preterm infants with GA ≤28 weeks. Patients will be randomized in a 1:1 ratio to receive either UCBa transfusion or standard treatment with adult-donor RBC.

The study will be conducted at three hospitals: The University and Polytechnic Hospital La Fe (Valencia, Spain), the University Clinical Hospital of Santiago (Santiago, Spain), and the Maternal and Child University Hospital Complex of Las Palmas (Las Palmas, Spain). The protocol was written following the Standard Protocol Items: Recommendations for Interventional Trials (SPIRIT) guidelines. The study was registered at European Union Drug Regulating Authorities Clinical Trials Database (EudraCT) with the identifier number 2022-003821-22. Figure 1 shows the SPIRIT flow diagram of the study.

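### Randomisation is stratified by gestational age, but the stated test and risk difference ignore that stratum; the test stays valid but is slightly conservative

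*Protocol article*

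**What the plan says.** Under Randomization and blinding, one stratification factor is named: "Randomization will be stratified into two groups by gestational age (GA"), with groups of 23–25 and 26–28 weeks and allocation in blocks. Centre is not named. Two sentences there bear on the list structure and point in different directions. The first, "Patient numbers will be assigned sequentially by order of entry into the study", reads like one common sequence. The second, "The Biostatistics Unit will provide a randomization list for the corresponding Neonatology Service containing the patient number", could mean a separate list for each hospital. The Study design section says "The study will be conducted at three hospitals".

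Under Statistical analysis, the rule for categorical variables begins "If the application assumptions are met, they are compared with" and goes on to name Pearson's chi-square test, with Fisher's exact test as the fallback. The effect measure is the risk difference with a 95% CI. No GA or centre term appears in the test or in the effect measure. The primary outcome is binary whether it is read as ROP (Primary outcome) or as death or ROP (Sample size calculation and power), so this rule governs it.

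**The concern.** Blocking within GA groups removes most chance imbalance in GA from the treatment comparison. A chi-square test on the pooled two-by-two table still counts the outcome variation between GA groups as random error. If GA is prognostic, and the Introduction ties ROP to the degree of prematurity, the test's standard error is then larger than the true sampling variation. The actual type I error falls below the nominal 5%, the unadjusted interval is somewhat too wide, and part of the precision gained by stratifying is lost. The article states a specific method that does not match its own randomisation, so this is more than a detail left for later.

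The list structure matters for the same reason: if each hospital has its own blocked lists, centre is a second randomisation factor that the stated test also ignores.

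**Working it through.** **The plan's own figure.** Inputs from Sample size calculation and power: 41% against 20.5% (a 50% reduction), alpha 0.05, power 0.80, N = 122, raised to 134. The pooled two-proportion formula gives 62 per arm (124 in total) one-sided and 79 per arm (158) two-sided. The stated 122 is therefore close only to a one-sided calculation. Two-sided power by formula is 69.4% at 122 and 73.5% at 134. These are the baselines below. The shortfall from 80% comes from the sample size and is a separate matter.

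**Assumptions (not in the documents).** One third of infants are in the lower GA group. Control event rates are either 65%/29% (strong GA effect) or 55%/34% (weaker). Both average to the stated 41%: 0.65/3 + 2 × 0.29/3 = 0.41, and 0.55/3 + 2 × 0.34/3 = 0.41. Treatment halves the risk in both groups. Tests are two-sided at 0.05.

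**Type I error by formula.** With allocation balanced within GA groups, the true variance per infant is the within-group average W = Σ w·p(1−p). The chi-square test uses M = p̄(1−p̄). Its z statistic then has standard deviation √(W/M), and the actual error is 2[1 − Φ(1.96/√(W/M))].
- Strong: W = 0.2275/3 + 2 × 0.2059/3 = 0.2131; M = 0.41 × 0.59 = 0.2419; ratio 0.881, root 0.939; 1.96/0.939 = 2.088; error 3.7%.
- Weaker: W = 0.2475/3 + 2 × 0.2244/3 = 0.2321; ratio 0.959, root 0.980; 1.96/0.980 = 2.001; error 4.5%.

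**Power by formula, N = 122 (61 per arm).** Power = Φ[(0.205 − 1.96 × SE₀)/SD]. SE₀ = √(2V/61), where V is the null variance that the test uses. SD is the true standard deviation with allocation balanced within GA groups.
- Chi-square, either case: V = 0.3075 × 0.6925 = 0.2129, SE₀ = 0.0836.
- Strong: SD = √((0.2131 + 0.1558)/61) = 0.0778. Chi-square power is Φ(0.530) = 70.2%. For the GA-stratified test V = 0.1967 and SE₀ = 0.0803, so power is Φ(0.612) = 73.0%. Gain 2.8 points.
- Weaker: SD = √((0.2321 + 0.1605)/61) = 0.0802. Chi-square power is Φ(0.514) = 69.6%. For the GA-stratified test V = 0.2074 and SE₀ = 0.0825, so power is Φ(0.540) = 70.6%. Gain about 0.9 points.

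**Simulation check.** 100,000 trials per setting, assumed blocks of 4 within GA group, no centre effect. CMH is the Cochran-Mantel-Haenszel test by GA group.

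| N | Assumed GA rates | Type I error, chi-square | Type I error, CMH | Power, chi-square | Power, CMH |
|---|---|---|---|---|---|
| 122 | 65%/29% | 3.9% | 4.8% | 70.6% | 73.5% |
| 134 | 65%/29% | 3.5% | 5.1% | 75.0% | 77.3% |
| 122 | 55%/34% | 4.8% | 5.0% | 69.8% | 70.8% |
| 134 | 55%/34% | 4.3% | 4.9% | 74.5% | 75.1% |
| 122 | 41%/41% | 5.4% | 5.4% | 69.8% | 69.9% |

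The formula and the simulation agree. The gain is 2–3 points with the strong GA effect, about 0.5–1 point with the weaker one, and nothing if GA is not prognostic.

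**Centre, for scale only.** Midpoints of the stated annual births are 6,250, 2,100 and 4,650, so the smallest hospital's share is 2,100/13,000 = 16%, or about 22 of 134 infants. Total births are only a proxy for births at 28 weeks or below. With one common list, an arm difference of 6 or more infants at that hospital would occur in about 17% of trials at N = 122. Centre-stratified allocation plus a centre-stratified test would gain about 0–1.5 points for no to moderate assumed spread in event rates between centres, 2–3 points for large spread, and 5–6 points only for extreme spread (control rates from 20% to 74%).

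**The case against.** The strongest reply is that nothing is invalid here. A conservative test does not raise the false-positive risk, the loss is small, and it rests on assumed GA rates. A journal article may also leave covariate adjustment to a fuller document. The first part stands: this is an efficiency point, not a validity defect. The second part stands only in part, because the article does not stay silent. It names the test and the effect measure, and neither uses the factor it randomises by.

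A reader might go further and infer three things about centre that the documents do not support.
- **That centre balance is left to chance.** The sentence about the list for each Neonatology Service may mean per-hospital lists, in which case centre is balanced by design. Even with a common list, chance imbalance is part of the sampling error that the test already covers; in simulation of centre effects alone the unstratified test kept its level (0.045–0.054).
- **That omitting centre wastes power.** No event rates by centre are given. Under a common list, adding centre to a GA-stratified test lost about 1–2 points in some runs. Evidence of differing practice is mixed: Study population refers to local transfusion guidelines, while Intervention cites one national recommendation (these passages need reconciling). One saturation target and one ROP classification apply to all.
- **That randomising by centre and GA together would be free.** 134/6 is about 22 per stratum on average, but the smallest hospital would have about 22 infants in all. With one third in the lower GA group, that stratum would hold about 7. Stratifying by GA alone is a defensible choice in a trial of this size.

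**Conclusion.** The point holds as a minor improvement. The stated primary comparison does not use the GA groups by which infants are randomised. Its type I error would be about 4% under a strong assumed GA effect, and the power given up is about 2–3 points in that case or 0.5–1 point under a weaker one. This rests on the assumed GA rates, the assumed one-third share in the lower group, and two-sided testing. The loss is far smaller than the gap between about 69% and the planned 80%, which the sample size causes. On centre, the only supported conclusion is that the article does not make clear whether lists are per hospital. If they are, the same mismatch applies to centre: with control rates assumed to run from 20% to 74% across hospitals, and no GA effect, the chi-square error would fall to 3.7% at N = 122 and 3.2% at N = 134.

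**What to change.** - Make the primary comparison a Cochran-Mantel-Haenszel test stratified by GA group (23–25, 26–28). Report a matching stratified risk difference with its 95% CI in place of the unadjusted one. A regression-standardised risk difference adjusted for GA group is an acceptable alternative.
- Specify this before unblinding. The unadjusted chi-square result can be kept as a supportive analysis.
- State under Randomization and blinding whether the blocked lists are common or issued per hospital. If per hospital, add centre to the stratified analysis. If common, adjustment for centre is optional and, if wanted, should be fixed in advance.
- Leave the randomisation lists as they are.

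The cost is wording only: no new data, no new lists and no change in sample size. If GA proves not to be prognostic, stratifying on two groups costs essentially nothing (69.9% against 69.8% power at N = 122).
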